## Abstract

**Background:**

Ethiopia is one of the ten countries in the world that together account for almost 60% of all maternal deaths. Recent reductions in maternal mortality have been seen, yet just 26% of women who gave birth in Ethiopia in 2016 reported doing so at a health facility. Maternity waiting homes (MWHs) have been introduced to overcome geographical and financial barriers to institutional births but there is no conclusive evidence as to their effectiveness. We aim to evaluate the effects of upgraded MWHs and local leader training in increasing institutional births in the Jimma zone of Ethiopia.

**Methods:**

A parallel, three-arm, stratified, cluster-randomized controlled trial design is being employed to evaluate intervention effects on institutional births, which is the primary outcome. Trial arms are: (1) upgraded MWH + religious/community leader training; (2) leader training alone; and (3) standard care. Twenty-four primary health care unit catchment areas (clusters) have been randomized and 3840 women of reproductive age who had a pregnancy outcome (livebirth, stillbirth or abortion) are being randomly recruited for each survey round. Outcome assessments will be made using repeat cross-sectional surveys at baseline and 24 months postintervention. An intention to treat approach will be used and the primary outcome analysed using generalized linear mixed models with a random effect for cluster and time. A cost-effectiveness analysis will also be conducted from a societal perspective.

**Discussion:**

This is one of the first trials to evaluate the effectiveness of upgraded MWHs and will provide much needed evidence to policy makers about aspects of functionality and the community engagement required as they scale-up this programme in Ethiopia.

**Trial registration:**

ClinicalTrial.gov, NCT03299491. Retrospectively registered on 3 October 2017.

## Background

The recently established Sustainable Development Goals reaffirm a global commitment to reducing maternal mortality [1]. Significant progress was made in reducing maternal mortality worldwide during the Millennium Development Goal period from 1990 to 2015; however, levels remain unacceptably high and large regional disparities exist. Globally, maternal mortality in 2015 was 216 per 100,000 livebirths, while in sub-Saharan Africa the rate was more than double this (546 per 100,000 livebirths). Ethiopia is one of the ten countries in the world that together account for almost 60% of all maternal deaths [2].

The majority of maternal deaths are preventable if women have timely access to good-quality maternal health-care services. Access to skilled obstetric care during and soon after birth is critical for the survival of women. However, in Ethiopia, only 26% of women who gave birth in 2016 reported doing so at a health facility [3]. In fact, over 40% of births were overseen by traditional birth attendants and in 15% women were entirely on their own [3]. Obstetric services are provided at the health centre and hospital level but are not available at community-based health posts.

Several barriers have been identified in rural sub-Saharan African that can impact a woman’s ability to access skilled obstetric care. These include barriers in the decision to seek care, barriers in reaching care, and barriers in receiving quality care once they arrive at a health facility, commonly referred to as the “three delays” [4]. Community-based interventions are often implemented to address the first two barriers [5–7], while the third barrier requires health system improvement on several levels [8].

Geographical and financial barriers are frequently cited as barriers to reaching skilled obstetric care during and after birth [9]. Women regularly have to travel large distances across difficult terrain, often made impassable during the rainy seasons, to get to health facilities [10]. Transportation options are frequently limited and may be expensive, leading to a limiting effect on the utilization of obstetric care [11]. Community-based surveys in Ethiopia report that women who live closer to health facilities are more likely to give birth there; for instance, women who are within a 1-h walking distance have 3.3 times higher odds of delivering at a health facility [12].

To address physical accessibility issues, particularly in rural areas where health facilities equipped with emergency obstetric services are sparsely distributed, maternity waiting homes (MWHs) have been constructed near or within health facilities. Women approaching their delivery date who will have difficulty in reaching a health facility on time are temporarily accommodated in these “homes away from home”. Women who are at a high risk for complications during delivery, such as very young mothers, women expecting twins, and those diagnosed with conditions such as high blood pressure, are also often referred to MWHs [13].

In Ethiopia, the Federal Ministry of Health has developed explicit guidelines pertaining to MWHs that outline referral criteria, minimum standards for accommodation and services to be provided, strategies to mobilize community contributions, and roles of various levels of government in managing MWHs. The challenge, however, lies with implementation and providing an acceptable level of service quality. A national facility assessment in 2012 on all MWHs listed in Federal Ministry of Health records found that the majority of MWHs did not provide food and did not have attendants to clean and maintain the MWHs [14]. Lack of space to accommodate relatives who were relied upon for food supplies and the absence of staff at night and during weekends were among the complaints made. The quality of MWH facilities has also been shown to affect institutional delivery rates in other African countries [15]. Women also expect health workers to check on them while they are at the MWHs and to assist with transfer to delivery rooms when they go into labour. With the effort and expense it takes to come to the MWHs, an absence of antenatal care support at an MWH could make staying at home a preferable option [16].

Community and religious leaders have been reported to be invaluable in mobilizing communities in order to improve access to health services in Ethiopia [17]. Additionally, given the prominent role of community contextual factors such as social norms around institutional births, community beliefs and expectations, and autonomy of decision-making by women, engaging local leaders in efforts to improve the access to care for women is crucial [9, 18].

This cluster-randomized trial is designed to evaluate the effects of upgraded MWHs and local leader training combined, or local leader training alone, versus usual care on the number of institutional births. We hypothesize that both interventions will increase the proportion of women who have institutional births, with the combined intervention expected to result in a greater increase. As secondary objectives, we will evaluate the effect of the interventions on antenatal care and postnatal care utilization and compare the costs and health outcomes associated with each intervention from the societal perspective.

## Methods

### Setting

The trial is being conducted in three rural districts (Gomma, Seka Chekorsa and Kersa) in the Jimma zone located in southwestern Ethiopia. These districts were selected from among the 18 districts located in the Jimma zone because: 1) they had the largest available populations; 2) MWHs were present at health centres; and 3) they did not have any active maternal and child health interventions at the time.

### Intervention components

Two interventions are being evaluated in the trial: upgraded MWHs and local leader training combined, and local leader training alone.

#### Upgraded MWHs

Existing MWHs will be provided with supplies to create a home-like environment suitable for pregnant women to reside in prior to delivery. The supplies provided were selected based on a review of existing literature, a rapid-needs assessment conducted at baseline, and input from the Jimma Zone Health Office (JZHO). Eleven indicators are used to specify the minimum required services at MWHs and these include room(s) with the capacity for at least 10 women, bedding, a kitchen with a chimney, a food supply, materials for the coffee ceremony (an important cultural routine for families), a clean water supply, a power source, toilet facilities, a bathing area, an attendant for the MWH, and follow-up by a skilled birth attendant. Items supplied are listed in Table 1.

**Table 1 Tab1:** Supplies provided to upgrade maternity waiting homes (MWHs) as part of the MWH intervention component

Bedding	Utensils	Personal hygiene	Other
Mattresses	Coffee grinder	Bath towels	Solar lamps
Bed sheets	Glasses	Buckets	Water tank (1000 l)
Pillows	Plates	Slippers	Cooking stove
Blankets	Water jug	Soap	Broom
	Coffee cups	Washing powder	Plastic floor sheets
	Coffee pot	Sanitary pads	Mop
	Local bread pan		Bleach
	Pots		Drinking water purifier

A register was also codesigned with the JZHO and introduced to facilitate tracking of MWH users and services provided as outlined in the national MWH policy guideline. The register is managed by antenatal care nurses who refer women to MWHs and are responsible for monitoring pregnant users during their stay prior to delivery. Funds are also provided to employ an attendant to clean the MWH, prepare meals and assist users during their stay at the MWH.

#### Local leader training

Community-based health extension workers (HEWs), religious leaders, and community leaders (specifically the Women’s Development Army) are targeted for the training workshops. The training aims to facilitate identification of barriers to accessing maternal health-care services and strategies to overcome these. The workshops use participatory learning methods that build on individual experiences. HEWs, who are employed by the Ethiopian health system, are invited to attend 3-day workshops while religious and local leaders attend 1-day workshops. Content for the workshops were developed by the research team based on barriers to care identified in the Three Delay Model and through formative, qualitative research carried out in 2016 [19]. Leaders are expected to integrate what they learn into their routine engagement with the communities to promote safe motherhood practices including accessing maternal health-care services and use of MWHs.

### Standard care (control group)

MWHs were officially introduced around 2013 and have gradually been scaled up across the country. These are modelled as a community–government partnership with a significant reliance on community contributions for their sustainability. Communities make both cash and in-kind contributions in the form of coffee and/or food. There is large variation in the availability of supplies and quality of services provided amongst MWHs. This is partly due to a fluctuation in resources available during the year among families and partly due to a weak management system. No records are maintained of MWH users and, in practice, there is very little monitoring of women who stay at these facilities. JZHO data suggest that, at baseline, the majority of MWHs in the study area were either very poorly or poorly functional based on the 11 service indicators. The national guidelines specify that women who live at a distance from health facilities or cannot be reached by ambulance or are 38 weeks pregnant or more and at risk of experiencing obstetric complications should be referred for MWH stay [20]. However, women are typically referred to MWHs when they present with false labour or arrive at the very early stages of labour. A smaller proportion of women are referred to MWHs by antenatal care nurses if they live very far away from a health centre and are expected to deliver in a few weeks. Referral practices vary among health centres and staff.

Health promotion activities are mainly conducted by HEWs who are sometimes assisted by members of the Women’s Development Army. Although some religious leaders may encourage their community members to deliver at health facilities, this is not a widespread or systematic practice in the study districts.

### Trial design

This study is a parallel, three-arm, stratified, cluster-randomized controlled, superiority trial with 24 clusters. The trial arms are as follows: 1) upgraded MWH + leader training; 2) leader training alone; and 3) standard care. Primary health-care unit (PHCU) catchment areas were designated as clusters for the trial. PHCUs are composed of a health centre and satellite health posts; health posts operate in the community, covering a population of 3000–5000 and are each managed by two to three HEWs. MWHs are located within health centres as standalone structures or in the form of a room assigned to function as an MWH. Outcome assessments will be made using repeat cross-sectional surveys at baseline (prior to intervention roll-out) and at 24 months postintervention (i.e. the endline). A schematic for the trial design is displayed in Fig. 1. A cluster-randomized design was selected because the interventions are delivered at the health facility and community level which precludes individual-level randomization.

**Fig. 1 Fig1:**
[figure not shown]
Schematic of trial design. BEmOC basic emergency obstetric care, MWH maternity waiting home

### Cluster and individual selection

PHCUs were eligible for trial participation if health centres had a standalone MWH or a room designated for this purpose. All 26 health units in the three districts were eligible and 24 were randomly selected for the trial using a random number generator in STATA v13.

Women of reproductive age were eligible to participate in the trial if they were living in the villages within the selected PHCU catchment areas and had a pregnancy outcome (livebirth, stillbirth, spontaneous/induced abortion) up to 12 months prior to a survey round; baseline surveys commenced in October 2016 and endline surveys are scheduled to begin in April 2019. Lists of pregnant women registered by HEWs at health posts and Women’s Development Army volunteers within villages (‘*kebeles*’) function as the sampling frame for selection of eligible women at each survey time point. Names of women, their village of residence and their date of delivery organized by PHCU are included in the sampling frame. Random numbers generated in STATA v13 were assigned to each woman in the list, ranked, and then the required number sequentially selected. Since women were not excluded based on prior participation in surveys, it is possible that there is some overlap of participation in baseline and endline surveys, but the probability is expected to be low.

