### Outcomes

The primary outcome is self-reported institutional birth defined as delivery of the last child at a health facility where obstetric care is provided (i.e. health centre or hospital) as reported by an enrolled woman. Births at home, en route to a facility or at a health post will not be considered an institutional birth.

Two other maternal health-care service outcomes will be assessed: 1) antenatal care and 2) postnatal care. Self-reported antenatal care received for last child delivered as well as the total number of antenatal care visits made will be assessed. Self-reported postnatal care received for the last child delivered within 48 h and 6 weeks will be assessed as secondary outcomes.

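### Women can enter through an abortion, but the outcomes refer to the last child delivered and are not tied to the qualifying pregnancy, so some may contribute an older, unexposed birth or no outcome

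*Protocol article*

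**What the plan says.** Under Cluster and individual selection, the protocol article admits women who "had a pregnancy outcome (livebirth, stillbirth, spontaneous/induced abortion) up to 12 months prior to a survey round". The Methods paragraph of the abstract repeats this and counts all such women towards the sample: "3840 women of reproductive age who had a pregnancy outcome (livebirth, stillbirth or abortion) are being randomly recruited for each survey round".

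Under Outcomes, the primary outcome is "self-reported institutional birth defined as delivery of the last child at a health facility where obstetric care is provided". The same section lists what does not count: "Births at home, en route to a facility or at a health post will not be considered an institutional birth". Antenatal care is defined in parallel, as "Self-reported antenatal care received for last child delivered", and postnatal care likewise refers to the last child delivered. None of these definitions mentions the pregnancy through which the woman qualified or the 12-month window. The article gives no rule for a woman whose qualifying pregnancy ended in abortion, and it does not remove her from the primary analysis.

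On the frame from which women are drawn: "Names of women, their village of residence and their date of delivery organized by PHCU are included in the sampling frame". The lists are of pregnant women registered by health extension workers and Women's Development Army volunteers.

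**The concern.** Both definitions are fixed in the article, and they do not describe the same event. Eligibility turns on a recent pregnancy outcome of any kind. The outcome turns on the most recent delivery, whenever it took place. For a woman with a recent livebirth the two coincide, and a recent stillbirth also involves a delivery. For a woman with a recent abortion they separate: her last delivery is an older one, or there is none.

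If the older delivery took place before the intervention started, neither intervention could have influenced it. Such a woman still takes one of the 160 places per primary health-care unit and round, and she pulls the arm difference towards zero. The denominator is then no longer the births of the survey window, although the hypothesis concerns institutional birth under the interventions.

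**Working it through.** **Timing.** Under Participant timeline, upgraded homes were operational in June 2017. Under Trial status, endline runs from April to July 2019. Qualifying events at endline therefore fall between about April 2018 and July 2019, which is roughly 10 to 25 months after June 2017. For a woman who qualified through abortion, a previous birth further back than that interval is unexposed; a more recent one is exposed.

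**Inputs (Sample size section).** Control proportion 0.40; difference 0.17, so 0.57 in the intervention arm; two-sided alpha 0.025; power 80%; within-period ICC 0.1; cluster autocorrelation 0.8; 8 units per arm with 160 women each, so 1280 per arm and round.

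**The plan's own figure.**
- d_c = 1 + 159 × 0.1 = 16.9.
- r = 160 × 0.1 × 0.8 / 16.9 = 0.757.
- d_r = 1 − 0.757² = 0.426.
- Product d_c × d_r = 7.205.
- Individually randomised n per arm is 163 without and 175 with continuity correction. 163 × 7.205 = 1174, or 7.34 units; 175 × 7.205 = 1261, or 7.88 units. Both round up to 8, so the stated sample size is reproduced.

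**Power at 8 units, no dilution.** SE = √[(0.40 × 0.60 + 0.57 × 0.43) × 7.205 / 1280] = √[0.4851 × 7.205 / 1280] = 0.0523, and 0.17 / SE = 3.25. With critical value 2.241 the normal approximation gives 84.4%. With a noncentral t on 21 df (24 clusters less 3 arms, an assumed stand-in for the Kenward–Roger df) it gives 79.2%.

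**Worst-case dilution.** Let a be the share of sampled women who qualified through abortion. Suppose all of them have an earlier birth and all those births are unexposed, at 0.40 in every arm. The intervention-arm proportion is then 0.57(1 − a) + 0.40a, and the difference is 0.17(1 − a). The values of a are assumptions, because the article gives none.

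| a | Difference | Power, normal | Power, t(21) |
|---|---|---|---|
| 0% | 0.170 | 84.4% | 79.2% |
| 1% | 0.168 | 83.6% | 78.3% |
| 2% | 0.167 | 82.8% | 77.4% |
| 5% | 0.162 | 80.1% | 74.5% |
| 10% | 0.153 | 75.2% | 69.3% |
| 15% | 0.145 | 69.7% | 63.7% |

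**If these women are left out instead.** The difference stays at 0.17 and the cluster-period size becomes 160(1 − a). At a = 10%, m = 144, d_c = 15.3, r = 0.753, d_r = 0.433, and the product is 6.626. SE = √[0.4851 × 6.626 / (8 × 144)] = 0.0528, and power is 83.6% (normal) or 78.3% (t). At a = 5% it is 84.0% or 78.8%; at a = 15%, 83.1% or 77.7%.

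**The case against.** The strongest reply is that the share may be very small. The frame consists of registered pregnant women and carries a date of delivery. A pregnancy lost before registration would not appear in it, so few abortions may be sampled. This stands: at 1 to 2% the worst-case loss is only one to two power points, and the upper rows of the range have no support in the article.

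A second reply is that the sensible handling is to leave such women out of the birth denominator, which costs almost nothing, and that this detail could sit in a fuller document. The first half is right and is the basis of the fix. The second half stands only in part, because the article does not merely stay silent: it states an outcome rule, and that rule, as worded, reaches back to an older birth.

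Three stronger readings are tempting and are not supported:
- A reader might infer that abortions are scored as non-institutional, and so become zeros that no intervention can change. The exclusion sentence speaks only of births in certain places; nothing says that an abortion is scored that way.
- A reader might infer that the older births are mostly pre-intervention. The dates show only that they may be. The article gives no birth intervals or parity, and a birth 10 to 25 months earlier could fall after June 2017.
- A reader might infer a bias that could produce a false positive. The dilution described here acts towards the null, so it is a loss of power and of clarity about what is estimated.

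**Conclusion.** The mismatch between eligibility and outcome is real and lies in the stated definitions. Its effect on the primary comparison is conditional. It depends on the share of women who qualified through abortion, which is not documented, on how many of their earlier births were unexposed, and on such women being kept in the analysis with that earlier birth. The factor (1 − a) is therefore an upper limit on dilution for a given share: negligible at 1 to 2%, about four to five power points at 5%, and about nine to ten at 10%. Women who have never delivered have no outcome under the definition, whatever the share. Severity is moderate: the expected loss may be small, but the primary denominator should not be left to be settled once endline data are in hand.

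**What to change.** Define the primary, antenatal and postnatal outcomes on the index pregnancy, meaning the one that ended in the 12 months before the survey. Restrict the primary analysis denominator, at baseline and at endline, to index pregnancies that ended in a livebirth or stillbirth. Report the number of women who qualified through abortion by arm and round, descriptively only; this also shows how large the share was.

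The cost is a change of wording and an analysis filter. The questionnaire already has a section on reproductive history, so no new data collection should be needed. The sample becomes slightly smaller: for a share of up to 10%, power falls by about one point or less (84.4% to 83.6% normal, 79.2% to 78.3% with t on 21 df). The change should be made before the endline analysis.

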### Intervention assignment and masking

Stratification was employed to ensure a balanced distribution of poorly functioning MWHs and low basic emergency obstetric care (BEmOC) capacity health centres between the trial arms. JZHO data on MWH functionality assessed using the 11 indicators were used to classify clusters as high functioning (≥5 of 11 MWH indicators present) or low functioning (<5 of 11 MWH indicators present). Clusters were also grouped based on their capacity to provide BEmOC; high-capacity clusters were those that had at least 5 of the 7 signal functions present while low-capacity clusters had less than 5 signal functions present according to 2016 JZHO data. Signal functions are essential obstetric interventions, such as provision of parenteral anticonvulsants, necessary to prevent maternal deaths; they are used to assess the level of obstetric care provided at health facilities [21].

Clusters were stratified into four groups based on these strata (low MWH + low BEmOC; low MWH + high BEmOC; high MWH + low BEmOC; high MWH + high BEmOC). Within each stratum, a random number generator in STATA was used to generate the allocation schedule. The allocation sequence was generated by [name] who was not involved in implementing the trial and it was shared in a password-protected document with the principal investigator in Ethiopia ([name]) who was also not involved in recruitment and enrolment of clusters or individuals. Random allocation of clusters to trial arms took place once all clusters had been recruited for the study.

Interviewers collecting outcome data are blind to intervention assignment. Due to the nature of the intervention it is not possible to blind women or health-care providers at PHCUs to their intervention status. However, all women and health-care providers are blind to the study hypotheses. The consent for data collection includes a general description of the overall aims of the study (namely to understand the experiences of women when they are pregnant, giving birth and after delivery and to look for ways to make this safer for women and their babies), but women are not aware of their cluster’s allocation to the intervention or control arms.

